### Medication

The definition of the four different classes of medication is described in detail in Additional file 1. We include antidepressants, bisphosphonates, RAS-inhibitors and lipid lowering drugs. Patients switching within a drug class are excluded. For example when a patient switches from an ACE inhibitor to an Angiotensin II antagonist, the patient is not selected.

### Ethics

The Medical Ethics Review Committee (METC) of the University Medical Centre Utrecht has considered our research proposal in a meeting 13 July 2010 and concluded that the Dutch Medical Research Involving Human Subjects Act (WMO) was not applicable. Consequently the protocol was submitted to the Institutional Review Board (IRB) of UPPER, Utrecht University and they approved the study protocol. The trial was registered at http://www.trialregister.nl under the identifier NTR3237.

### Usual care

Usual care in most Dutch pharmacies is as follows: at the presentation of a first prescription for new medication, the pharmacist or technician provides the patients with spoken and written information about the medication and the disease. Instruction protocols are available and can be used. A first prescription is generally provided for a maximum of two weeks. Guidelines recommend that at the first refill, patients are asked about their experiences with the medication. If necessary, additional information or counselling should be provided. Guidelines for counselling at the first refill, however, are not generally implemented.

### Intervention

The intervention consists of a counselling call by a pharmacist or a competent technician in addition to usual care. The call is supported by a pre-tested interview protocol. For all medication groups a protocol is developed that describes the specific instructions or side effects for that specific group. For example for antidepressants it is mentioned that it can take up to 4–6 weeks to notice an effect. In Additional file 2 a translated version is presented. The focus in the protocol lies on both practical and perceptual barriers to take medication. The need for information about the indication, instructions, side effects and treatment plan will be assessed. Also concerns about the treatment, side effects and dependence will be discussed. The pharmacist will also inquire about the experiences with medication intake during the first 2 weeks of treatment (for example if the patient managed to take the medication, or experienced any possible side effect). The call takes place 7 to 21 days after the first prescription. If necessary the pharmacist will provide information, motivate the patient, help the patient to find a strategy to be adherent or refer the patient to the physician. After the telephone call the pharmacist registers all topics that have been discussed in an online database.

### Follow up

Dispensing data will be extracted from the pharmacy information system. In The Netherlands all prescriptions are registered in an administrative database, including date of prescription, number of prescribed tablets, prescriber and dosage regimen. A selection of pharmacies will collect data on patient beliefs and satisfaction with information and pharmacy counselling through a written questionnaire. In the selected pharmacies a questionnaire will be sent to patients in both arms, three months after the first prescription. The timeline per patient is shown in Figure 2.

**Figure 2 F2:**
[figure not shown]
Timeline per patient.

### Qualitative analysis of calls

To assess to which extent the pharmacist explores barriers that negatively influence adherence we will record a sample of telephone consultations. These recordings allow a direct analysis of communication without relying on participant reports or simulated situations [23]. In an amendment the Institutional Review Board of the division of Pharmacoepidemiology and Clinical Pharmacology of Utrecht University approved the collection of data.

Patients in the intervention arm meeting all eligibility criteria who give informed consent, are asked for permission to record the consultation.

### Outcomes

#### Primary outcome

The primary outcome is the proportion of adherent patients, based on refill adherence. Refill adherence will be calculated as proportion of days covered over the 360 days following the index date by dividing the total days’ supply by the number of days of study participation (PDC360) [24].

The index date is the date of the first prescription. The total days supplied will be calculated as the sum of days dispensed within the study period. If a supply exceeds the end of the study participation, this supply will be corrected for exceeding the end of the period. The number of days of study participation is defined as the number of days between the index date and the index date + 360 or the last refill date, whichever comes first. For assessing the last refill date, all refills for any drug will be included. We analyse refill adherence both as a continuous measure and as a dichotomous measure with a threshold of 80%. Patients with a PDC360 < 80% are defined as non-adherent and patients with a PDC360 ≥ 80% are defined as adherent.

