#### Secondary outcomes

##### Discontinuation

Discontinuation is defined as having a gap of more than 89 days with no medication available within the one year observation period. Cox-proportional hazards will be used to compare discontinuation rates between intervention and control patients.

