## Discussion

This is the first large intervention trial in The Netherlands to study the effect of telephone counselling by pharmacists on adherence. Although pharmacist can play an important role in improving adherence, in daily practice not all patients receive optimal care. The studied intervention is a way to deliver patient-centred care. And can be a solution to barriers in daily practice and that therefore more patients receive appropriate care. We also recognize that this intervention might not be appropriate for every individual patient, by including sufficient patients in 4 medication groups we expect to gain insight into which patients benefit most of this intervention.

The quality of the intervention depends on the competences and skills of the pharmacist. We try to assure treatment integrity by providing an interview protocol, an obligatory communication training and the obligation to document every counselling-call in an online database. Although it is likely that there will remain some differences between pharmacists, our goal is not to study the effect of an intervention in an ideal, perfectly controlled situation, but to study it in daily practice. We believe that this increases the external validity since it reflects current practice. The qualitative analysis of (a sample of) the telephone calls, will provide more insight in the intervention as provided by different pharmacists.

The intervention focusses on patient starting treatment and the aim of the intervention is to assess both practical and perceptual barriers that can influence adherent behaviour. These barriers can both be intentional or non-intentional and especially at the start of therapy it can be a mix of both. Moreover a recent study suggests that unintentional non-adherence is influenced by medication beliefs, chronic disease and socio-demographics [33]. So before a health care provider can tailor the intervention to intentional or non-intentional non-adherent behaviour, the barriers should first be assessed.

Assessment of adherence will be based on pharmacy data. Studies show that this is a valid method. In the Netherlands most prescriptions are filled for three months, irrespective of the frequency of dosing. Therefore, we expect to find enough contrast to assess the effect of the intervention on refill adherence.

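### The primary outcome is named proportion of days covered but is calculated as a summed-supply ratio, so overlapping supply after a within-class switch can be counted twice and hide gaps

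*Protocol article*

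**What the plan says.** The protocol article, Primary outcome, gives the measure its name: "Refill adherence will be calculated as proportion of days covered over the 360 days following the index date". The same section then defines it as total days' supply divided by days of study participation, and fixes the numerator: "The total days supplied will be calculated as the sum of days dispensed within the study period". One correction follows: "If a supply exceeds the end of the study participation, this supply will be corrected for exceeding the end of the period". No rule covers overlapping supplies, and there is no cap at 100%.

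The denominator runs from the index date to day 360 or to the last refill of any drug, whichever is earlier. The ratio is cut at 80%: "Patients with a PDC360 < 80% are defined as non-adherent". It is also analysed as a continuous measure, with a Mann–Whitney test under Statistical analysis.

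Four other places bear on the point:

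- Usual care says that a first supply is generally two weeks at most.
- The Discussion says: "In the Netherlands most prescriptions are filled for three months, irrespective of the frequency of dosing".
- Exclusion criteria and Medication exclude within-class switchers when patients are selected. The first limits this to the 12 months before inclusion, and the second gives an example of a patient who is not selected.
- The secondary outcome rests on calendar gaps: "Discontinuation is defined as having a gap of more than 89 days with no medication available within the one year observation period".

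**The concern.** A proportion of days covered asks, for each calendar day, whether the patient had medication. A sum of dispensed days does not ask that. When a patient switches within the class shortly after a three-month fill, the unused part of the old supply stays in the sum, and the new supply is added for the same days. The surplus then offsets later days with no medication at all.

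Patients who switch after the index date remain in the intention-to-treat analysis, because the switching exclusions act only at selection. At stake is whether the 80% cut separates patients by coverage, as the outcome's name promises. One patient could be adherent on the primary outcome and discontinued on the secondary outcome. The continuous analysis is affected too, since the overlap enters the value that is ranked.

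**Working it through.** The plan gives no figure for overlap or switching, so there is none to reproduce. The check uses its own supply lengths and definitions.

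**Inputs.** First supply 14 days (Usual care). Later supplies three months, taken as 90 days (Discussion). Full participation 360 days and threshold 80% (Primary outcome), so 0.80 × 360 = 288 days. Assumptions: supply is summed across the class, and the dispensing schedule is as below.

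**Schedule.** Old drug: 14 days on day 0, 90 days on day 14 (lasting through day 103). Switch on day 30. New drug: 14 days on day 30, 90 days on day 44, 90 days on day 134 (lasting through day 223). The patient then stops. Some other drug is still refilled on or after day 360, so the denominator is 360.

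**As the article defines it.** 14 + 90 + 14 + 90 + 90 = 298, and 298/360 = 82.8%: adherent.

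**Each calendar day counted once.** 30 + 14 + 90 + 90 = 224, and 224/360 = 62.2%: non-adherent. The difference is the overlap on days 30 to 103, which is 74 days (298 − 224 = 74), or 20.6 points.

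**Against the secondary outcome.** The uncovered run is 360 − 224 = 136 days. That exceeds 89, so this patient counts as discontinued.

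**Dependence on the denominator.** Let D be the last refill of any drug, up to 360.

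- Coverage falls below 80% only if 224/D < 0.80, that is D > 280.
- Summed supply stays at or above 80% for every D up to 298/0.80 = 372.5, so for every possible D.
- The two methods therefore disagree only for D above 280.
- If the last refill of any drug is on day 134, truncated supply is 14 + 90 + 14 + 90 = 208. Then 208/134 = 155% and coverage is 134/134 = 100%. Both methods call the patient adherent.

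**Dependence on the switch day.** After a 90-day fill on day 14, the overlap for a switch on day d is 104 − d days:

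- day 21: 83 days (23.1 points of 360)
- day 30: 74 days (20.6 points)
- day 60: 44 days (12.2 points)
- day 90: 14 days (3.9 points)

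A switch on day 14, before that fill is collected, creates no overlap.

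**Exceeding 100%.** Old drug as above, switch on day 21, then 90 days of the new drug on days 21, 111 and 201: 14 + 90 + 90 + 90 + 90 = 374, and 374/360 = 103.9%. Days covered are 201 + 90 = 291, and 291/360 = 80.8%. Both are adherent at 80%, but the continuous values differ by 23.1 points.

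**The case against.** The strongest reply is that overlap and capping rules are programming detail, which a condensed article leaves to the full protocol or analysis plan, and that a cited source for the measure cannot be seen here. This would answer a complaint that a rule is missing. It does not answer this point, because the article states the rule: a plain sum with one named correction. A plan that counted each day once would contradict it.

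Other objections stand in part:

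- The example needs a late refill of another drug, as shown above. Without one, nobody is misclassified.
- Summation across the class is an inference. The detailed class definitions are in Additional file 1, which is not shown.
- Surplus from early refills of the same drug is real stock, and carrying it forward gives much the same answer.
- A ratio above 100% does not by itself change the classification at 80%.
- The discontinuation outcome would catch gaps as long as the one in the example, though not those of 89 days or less.

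A reader might go further and infer a bias in favour of the intervention: the caller may "help the patient to find a strategy to be adherent or refer the patient to the physician", referral may lead to switches, and switches inflate the ratio. The documents do not support that. They do not say that calls lead to switches, they list referral as one option among several, and they give no switch rate in either arm. Any figure would be the product of two invented inputs, the excess switching and the share misclassified. Even the sign is open. If supply is summed for the index drug only, switchers lose days and look non-adherent, and more switching in the intervention arm would then count against it.

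**Conclusion.** The name and the formula of the primary outcome do not match, and the formula can classify a patient with 62% coverage as adherent. That result assumes class-level summation, a switch soon after a three-month fill, and a refill of some drug after day 280. For individual switchers the overstatement is about 4 to 23 points of PDC360 for switches between day 90 and day 21 under the schedule used. How many patients are affected, and whether the arms differ, cannot be known from the documents. The size and direction of any effect on the treatment comparison are therefore unknown. This is an outcome definition that should be corrected, not a demonstrated bias in the trial's result.

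**What to change.** In Primary outcome, define PDC360 from a day-by-day indicator at medication-class level over the participation period as already defined:

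- Count each calendar day at most once, so that the value cannot exceed 100%.
- At a switch to another drug in the class, end the previous supply on the switch date.
- On an early refill of the same drug, carry the surplus forward.
- State explicitly that supply is assessed by class and not by index drug.

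The dispensing dates, quantities and dosage regimens needed are already in the records to be extracted (Follow up). The cost is some extra programming and slightly lower adherence estimates.

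### The PDC360 denominator ends at the last refill of any drug, so patients who refill on time and then stop all medication early count as adherent, and single-fill patients without other dispensing cannot be scored

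*Protocol article*

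**What the plan says.** The Primary outcome section of the protocol article sets the endpoint: "The primary outcome is the proportion of adherent patients, based on refill adherence", with a PDC360 of 80% or more counting as adherent. It introduces the measure as the "proportion of days covered over the 360 days following the index date" and fixes day 0: "The index date is the date of the first prescription".

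The denominator that follows is not always 360 days. Participation runs to day 360 "or the last refill date, whichever comes first. For assessing the last refill date, all refills for any drug will be included". The numerator is cut to match: "If a supply exceeds the end of the study participation, this supply will be corrected for exceeding the end of the period". The article gives no rule for a denominator of zero days.

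Four other places matter:
- Usual care gives the usual first supply: "A first prescription is generally provided for a maximum of two weeks".
- The Discussion says that most Dutch prescriptions are for three months.
- Recruitment of patients and Statistical analysis both commit the primary analysis to the intention-to-treat principle.
- The Discontinuation section has a window of its own: "Discontinuation is defined as having a gap of more than 89 days with no medication available within the one year observation period".

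**The concern.** For a patient who takes nothing else, the last refill date is set by the behaviour being measured. Someone who collects on time and then gives up has a clock that stops at the last collection. The untreated time after that date is not counted as uncovered; it is not counted at all. The Background names complete discontinuation as one of the stages of non-adherence, so the primary outcome can score as a success a failure that the call is meant to prevent.

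Two things follow. The same pattern of study-drug collection can be adherent in one patient and non-adherent in another, purely because the second still collects another medicine. And a patient with one fill and no other dispensing has no PDC360. Leaving such patients out would select the analysis set on post-randomisation behaviour, although the plan promises to analyse all eligible patients.

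**Working it through.** **Inputs.** First supply 14 days (upper limit in Usual care); later supplies 90 days (three months, Discussion); adherent at 80% or more; participation is "the number of days between the index date and the index date + 360 or the last refill date, whichever comes first" (Primary outcome).

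**Step 1: the plan's own figure.** The Sample size section states 294 per arm for 70% vs 80%, two-sided 0.05, power 0.80. With pooled variance and no continuity correction:
n = [1.96·√(2·0.75·0.25) + 0.8416·√(0.70·0.30 + 0.80·0.20)]² / 0.10² = 293.2, rounded up to 294. It is reproduced. It is used below only for the 70% and 80%.

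**Step 2: the scoring rule.**
- D = min(360, day of the last refill of any drug)
- Numerator = sum over study-drug fills of min(days supplied, D − fill day)
- PDC360 = numerator / D
- Comparison: the same formula with D = 360 for everyone.

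| Study-drug fills | Last refill of another drug | Rule as written | Fixed 360 days |
|---|---|---|---|
| 14 d at day 0 only | none | 0/0, undefined | 14/360 = 3.9% |
| 14 d at day 0, 90 d at day 14, stop | none | 14/14 = 100%, adherent | 104/360 = 28.9% |
| as above plus 90 d at day 104, stop | none | 104/104 = 100%, adherent | 194/360 = 53.9% |
| 14 d at day 0, 90 d at day 14, stop | day 350 | 104/350 = 29.7%, non-adherent | 28.9% |
| 14 d at day 0, 90 d at day 60, stop | none | 14/60 = 23.3%, non-adherent | 104/360 = 28.9% |
| fills at days 0, 14, 104, 194 and 284, all on time | none | 284/284 = 100%, adherent | 360/360 = 100% |

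Rows 2 and 4 have identical study-drug fills and opposite labels.

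**Step 3: where the label switches.** For the 14 + 90 day stopper, 104/D ≥ 0.80 holds when D ≤ 104/0.80 = 130. If another drug was last refilled on day 130 the score is 80.0%, adherent; on day 131 it is 79.4%, non-adherent. For the single 14-day fill the limit is 14/0.80 = 17.5 days: another drug last refilled on day 17 gives 14/17 = 82.4%, and on day 18 it gives 14/18 = 77.8%.

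**Step 4: illustration only.** Let f be the share of truly non-adherent patients affected, equal in both arms. The documents do not give f. Take 70% vs 80% to be adherence over the fixed window.
- If all are counted as adherent, observed p = p + (1 − p)·f. At f = 0.1: 73% vs 82%, a difference of 9 points. At f = 0.3: 79% vs 86%, 7 points.
- If all are dropped as 0/0, observed p = p / (1 − (1 − p)·f). At f = 0.1: 0.70/0.97 = 72.2% vs 0.80/0.98 = 81.6%, 9.5 points before rounding. At f = 0.3: 0.70/0.91 = 76.9% vs 0.80/0.94 = 85.1%, 8.2 points.

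**The case against.** The any-drug clause has a sensible purpose: it looks like a proxy for still being a customer of the pharmacy. The data items listed under Follow up do not include death or departure, so a fixed window would count silent leavers as non-adherent, which is also misclassification. This stands as a cost. It does not rescue the rule, which cannot tell a patient who has left from one who has stopped all medication.

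A reader might infer more than the documents support:
- **That all early stoppers count as adherent.** They do not. Rows 4 and 5 of the table show stoppers labelled correctly.
- **That the trial loses a definite amount of power.** The share f has no anchor in the documents. Some affected patients would be unscorable and not counted as adherent. The Sample size section says the calculation concerns the primary outcome; if 70% and 80% already refer to PDC360 as defined, the loss in Step 4 does not arise.
- **That the discontinuation outcome misses the same patients.** Its stated window is one year, and nothing ends it at the last refill. As written, it can pick these patients up.
- **That overlapping fills are counted twice.** Day-level handling of overlap is a detail that a condensed article may leave to the full plan.
- **That differences in co-medication between drug classes bias the comparison.** Arms are compared within the same drug class, so these differences do not by themselves bias the contrast.

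A zero-day rule may also exist in the full plan. The 100% score for all-medication stoppers, however, follows from a rule the article states outright.

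**Conclusion.** The point holds in a limited form. As written, PDC360 scores at or near 100% any patient who refills on time and then stops all medication early, with no later refill of another drug or only an early one. It gives no score to a patient with one fill and no other dispensing. For these patients the result contradicts the 360-day measure that the same section announces, and leaving out the unscorable ones would conflict with the intention-to-treat commitment.

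For an individual patient the error can be large: 100% against 28.9% or 53.9% in the examples. These rest on supplies of 14 and 90 days and on-time collection before stopping. For the trial as a whole the size is unknown. The shrinkage from 10 points to 9 or 7 points holds only if 10% to 30% of truly non-adherent patients were counted as adherent, equally in both arms, and if 70% vs 80% means fixed-window adherence. Nothing in the documents shows that the error differs between arms. Because the rule defines the primary endpoint and the correction uses the same dispensing data, it should be changed.

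**What to change.** - Use a fixed 360-day denominator for the primary PDC360 in every intention-to-treat patient. Count days without supply as uncovered, and score single-fill patients as non-adherent.
- Shorten follow-up only where death or departure from the pharmacy is actually recorded, and state whether the pharmacy system holds those records.
- Keep the last-refill rule as a sensitivity analysis, with a stated handling of zero-day denominators. The two results together bound the effect of patients who silently change pharmacy.
- State that the 89-day gap outcome uses the same full window, so that the primary outcome and the discontinuation outcome agree.

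The cost is one paragraph and a change to the PDC query, with no new dispensing data. The small downside is that silent pharmacy-changers count as non-adherent in the primary analysis, so reported adherence levels will look lower.
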